### 5.23. Statistical Analysis Methods

- Basic statistical methods

All statistical analyses will be conducted using SPSS 26.0 and GraphPad Prism 9.0 software, statistical analysis will be primarily descriptive. Quantitative data will be presented as median (interquartile range), and qualitative data will be presented as n (%). The differences between groups of quantitative data will be performed using student's t tests or Wilcoxon non-parametric tests. Qualitative variables will be tested with chi-square tests or Fisher's exact tests. The methods of Kaplan-Meier will be used to estimate the time-to-event data. All tests will be calculated with a two-sided significance level of 0.05.

- Safety analysis

Summary tables for adverse events have to include all AEs that occurred in the whole period of study. The correlation between treatment and AEs will be determined by the principal investigator.

- Effectiveness analysis

Proportions with 95% confidence intervals will be calculated for the efficacy endpoint.

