# 3. Objective and Endpoints of the Study

## 3.1 Objective of the Study

- Primary objective:

To observe the incidence of adverse events in patients after UC-MSCs infusion, and to preliminarily evaluate the safety of clinical infusion of UC-MSCs.

- Secondary objectives:

1. To preliminarily evaluate the effectiveness of UC-MSCs in the clinical treatment of refractory ITP patients;
2. To preliminarily evaluate the pharmacokinetics characteristic of UC-MSCs in patients with primary ITP;
3. To preliminarily evaluate the immunogenicity of UC-MSCs in patients with primary ITP;
4. To explore the changes in immune function before and after UC-MSC infusion.

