## 3.2 Study Endpoints

- Primary endpoint:

Safety endpoint: the safety and tolerance of UC-MSCs in patients with primary ITP. The safety and tolerance of UC-MSCs will be evaluated according to the incidence and severity of adverse events and serious adverse events (according to NCI CTCAE 5.0 standard).

- Secondary endpoints:

Effectiveness endpoints:

1. Platelet counts at each visit point to evaluate the response rate.
2. Percentage of subjects with platelet counts≥50×10^9^/L and ≥100×10^9^/L at least once respectively.
3. Percentage of subjects with platelet counts ≥ 30×10^9^/L and 2-fold increase from baseline at least once.
4. The time required from the first infusion to platelet counts first ≥ 50×10^9^/L.
5. Percentage of subjects receiving emergency treatment
6. Percentage of subjects with reduced concomitant medications.
7. The longest duration of the subject's platelet counts continuously ≥ 30×10^9^/L.
8. Changes in bleeding scores (WHO bleeding scores) throughout treatment.

Pharmacokinetic endpoint:

Pharmacokinetic characteristics of UC-MSCs in patients with primary ITP, especially the concentration changes of UC-MSCs in peripheral blood.

Immunogenicity endpoint:

Incidence of UC-MSCs antibodies.

Other study endpoints:

Changes in immune status in vivo after UC-MSCs infusion.

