# 5. Study Design and Statistical Methods

## 5.1 Study Design

This is a single-centre, open-label, single-arm study, which is divided into two-stage: dose-escalation stage, and dose-expansion stage.

In the dose-escalation stage, three successively increasing dose groups were set up, and the initial dose of the study was the lowest dose group. Subject enrollment, judgment and treatment of dose-limiting toxicity (DLT) refer to the traditional "3+3" dose-escalation design principle. That is, starting from the lowest dose group, 3 subjects were enrolled each time. If no DLT is observed, the trial will be continued at the next level dose; if DLT occurs in one of three patients, three more patients will be enrolled in the current dose, and when no DLT occurs anymore, the trial will be continued at the next level dose. If 2 or more DLTs occur in the 3 or 6 patients, the dose escalation will be stopped, and the current dose will be determined as the maximum tolerated dose (maximum tolerated dose, MTD). The flow of this trial is shown in Figure 1. Considering the safety of UC-MSCs, there will be 9 to 12 patients enrolled in the dose-escalation stage.

[figure not shown]
**Figure 1.** “3 + 3” dose-escalation protocol

[figure not shown]
The final dose in the dose-expansion phase will be determined based on the MTD in the dose-escalation phase, safety, efficacy, and opinion considered by the principal investigator, six patients will be enrolled in the dose-expansion stage to preliminarily explore the efficacy.

**Figure 2.** Six subjects will be enrolled to further evaluate the safety and efficacy of this dose infusion of umbilical cord MSCs

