## 14.2 Evaluation Criteria of Efficacy

- Main efficacy criteria:

umbilical cord-derived MSCs infusion can increase the platelet count of the subjects, indicating that the drug is effective.

Evaluation criteria of efficacy:

According to the international consensus of ITP:

- complete response (CR): platelet count ≥ 100 × 10^9^ /L and no bleeding after treatment.
- response (R): platelet count ≥ 30 × 10^9^ /L and at least doubling of the baseline count, and no bleeding after treatment.
- No response (NR): platelet count <30 × 10^9^ / L or less than doubling of the baseline count or bleeding after treatment.
- Relapse: platelet count below 30 × 10^9^/L, or less than doubling of the baseline count, or bleeding, after the achievement of CR or R.

When defining a CR or R, it should be tested at least twice with an interval of at least 7 days.

- Safety efficacy criteria:

The subjects have no obvious adverse reactions caused by umbilical cord-derived MSC infusion, normal vital signs, no hepatitis B, hepatitis C, and other virus infections, and no abnormal organ function. There was no significant difference (P > 0.05) in heart, liver, and renal function between objects before and after treatment, indicating that umbilical cord-derived MSCs have no obvious side effects and are safe.

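### Section 5.23 ties its t and Wilcoxon tests to differences between groups and names no paired method, yet the protocol's one P-value comparison (14.2, organ function before v after) is within the same subjects

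*Protocol*

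**What the plan says.** Section 5.1 sets the design: "This is a single-centre, open-label, single-arm study, which is divided into two-stage: dose-escalation stage, and dose-expansion stage". There is no control arm. The only groups are the three dose levels and the expansion cohort.

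Section 5.23 describes the analysis in general terms as follows: "statistical analysis will be primarily descriptive". For quantitative data it adds: "The differences between groups of quantitative data will be performed using student's t tests or Wilcoxon non-parametric tests". For categorical data: "Qualitative variables will be tested with chi-square tests or Fisher's exact tests". The error rate is set once: "All tests will be calculated with a two-sided significance level of 0.05". The protocol does not mention a paired t test, a signed-rank test or a repeated-measures model.

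Three places concern change within a subject:

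- Section 14.2, under the safety criteria, requires no significant difference (P > 0.05) "in heart, liver, and renal function between objects before and after treatment" and takes that result as showing that the cells are safe.
- Section 3.1, secondary objective 4: "To explore the changes in immune function before and after UC-MSC infusion".
- Section 3.2, effectiveness endpoint 8: "Changes in bleeding scores (WHO bleeding scores) throughout treatment".

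Only the first of these is tied to a P value.

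**The concern.** The method and the question do not match. Section 5.23 speaks of differences between groups, which in this trial would naturally mean the dose groups, yet no objective or endpoint asks for a comparison of doses. The comparison that section 14.2 does test sets each subject against that subject's own baseline.

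An analyst who follows 5.23 literally would treat the before and after columns as two unrelated samples. Stable differences between subjects then stay in the error term. When before and after values are positively correlated, the standard error is too large and the test rejects too seldom.

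In most settings that costs only efficiency. Here it also has a direction. Section 14.2 reads a non-significant result as evidence of safety, and safety is the primary objective, so a test that misses worsening more often makes the favourable conclusion easier to reach.

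**Working it through.** **Sample size.** Three dose groups of 3 plus 6 in expansion gives 3 × 3 + 6 = 15, which matches the minimum in section 7. With 12 in escalation the total is 12 + 6 = 18. The protocol states no power, SD, effect size or within-subject correlation, so there is no power figure to reproduce.

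**Inputs.** From the protocol: N = 15 and two-sided alpha 0.05. Assumed, and shown as a range: mean change d of 0.5, 0.8 or 1.0 between-subject SD; correlation ρ between before and after of 0 to 0.8; equal SDs; normal data.

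**Formulas.** With unit SD, the within-subject change has variance 2(1 − ρ). The paired t test therefore has noncentrality d√n / √(2(1 − ρ)) on n − 1 = 14 degrees of freedom, critical value 2.145. The independent-samples t test estimates the variance of the mean difference as about 2/n whatever ρ is, while the true variance is 2(1 − ρ)/n. It refers the result to 28 degrees of freedom, critical value 2.048.

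**Paired test, d = 0.5.** Here d√n = 0.5 × 3.873 = 1.936.

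- ρ = 0: 1.936 / √2.0 = 1.369, power 25%
- ρ = 0.2: 1.936 / √1.6 = 1.531, power 30%
- ρ = 0.5: 1.936 / √1.0 = 1.936, power 44%
- ρ = 0.7: 1.936 / √0.6 = 2.500, power 64%
- ρ = 0.8: 1.936 / √0.4 = 3.062, power 81%

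**Independent test.** Its behaviour on correlated data was simulated with bivariate normal before and after values, at least 40,000 trials per cell. The same simulations agree with the noncentral t values for the paired test.

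| Change | Correlation | Independent t | Paired t |
| --- | --- | --- | --- |
| 0.5 SD | 0 | 26% | 25% |
| 0.5 SD | 0.2 | 24% | 30% |
| 0.5 SD | 0.5 | 20% | 44% |
| 0.5 SD | 0.7 | 15% | 64% |
| 0.5 SD | 0.8 | 13% | 81% |
| 0.8 SD | 0.5 | 58% | 82% |
| 0.8 SD | 0.7 | 60% | 96% |
| 0.8 SD | 0.8 | 62% | 99.5% |
| 1.0 SD | 0.5 | 82% | 95% |
| 1.0 SD | 0.8 | 90% | above 99.9% |

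**No true change.** The independent test rejects in about 5% of trials at ρ = 0, 0.8% at ρ = 0.5 and 0.1% at ρ = 0.7, against a nominal 5%.

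**Rank tests.** The pattern is the same. At N = 15, d = 0.5 and ρ = 0.7, the Mann-Whitney test has 14% power and the signed-rank test 61% (3,000 trials).

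**Larger N.** At N = 18, d = 0.5 and ρ = 0.7 the figures are 21% and 73%.

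**The case against.** The strongest reply is that the protocol never prescribes an unpaired test on before and after data. Student's t and Wilcoxon both have paired forms, and the words independent, two-sample and rank-sum do not appear. Dose groups exist, so the sentence may simply be about them, and the form of a before-after test is the kind of detail that a statistical analysis plan can settle. This stands in part: loss of pairing follows from the words between groups but is not stated outright. What remains is that 5.23 gives the tests a scope that leaves out the one comparison 14.2 relies on. A separate analysis plan that named paired tests would still leave those two sections out of step.

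Several stronger readings are tempting, and the documents do not support them:

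- *Most within-subject changes would be missed.* This depends on effect size. At 0.8 to 1.0 SD and correlations of 0.5 to 0.8, even the independent test detects 58-90%.
- *Immune and bleeding-score effects would be hidden.* The protocol attaches no test to either, and the analysis is described as mainly descriptive.
- *Chi-square and Fisher tests are misapplied to before-after counts.* No binary before-after comparison is specified.
- *Pairing has no downside.* At N = 6, correlation 0.1 and a change of 1.0 SD, paired power is 32% against 34%; at 1.5 SD it is about 60% against 66%.
- *Pairing would make the rule in 14.2 sound.* It would not. At N = 15, 0.5 SD and correlation 0.5, the paired test still misses 56% of such changes (100 − 44).

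**Conclusion.** The point holds as a mismatch between 5.23 and 14.2, not as proof that the trial will run the wrong test. If the organ-function comparison is run as written, on independent samples, and if before and after values are positively correlated, the test is conservative and tilts the P > 0.05 rule towards a finding of safety.

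For a 0.5 SD change in 15 subjects the power given up runs from about 6 points at correlation 0.2 (30 − 24) to 68 points at 0.8 (81 − 13). For 0.8 SD it is 24 points at correlation 0.5 (82 − 58) and about 37 at 0.8 (99.5 − 62). Nothing is lost at zero correlation. All these figures rest on assumed effect sizes, correlations, equal SDs and normality.

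The reach is limited. The primary endpoint, incidence and severity of adverse events, and the efficacy proportions with their 95% CIs do not use these tests. The text is worth correcting because the error would favour the reassuring conclusion and the correction is cheap.

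**What to change.** Add to 5.23 wording to this effect: before-after comparisons of quantitative data (organ function in 14.2, and immune function and bleeding score if they are tested) use the within-subject change, with a paired t test or a Wilcoxon signed-rank test, and report the mean or median change with its 95% CI. State that the independent-samples forms are kept for comparisons between dose groups.

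In 14.2, let the CI for the change carry the safety reading, since it shows how much worsening the data do not exclude; a P value above 0.05 does not.

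The cost is a few lines of text. The data, visits and software stay the same. The only statistical price is a small loss of power if the correlation is near zero and the number of subjects is very small.

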# Inclusion, Exclusion Criteria and Assignment Methods

## 6.1 Inclusion Criteria

1. 18-60 years of age;
2. Confirmed diagnosis of ITP for at least 6 months with an insufficient response to first-line treatment drugs (IVIG, glucocorticoids), and thrombopoietic agents (recombinant human thrombopoietin (rhTPO), eltrombopag, avatrombopag, romiplostim, etc.) and anti-CD20 monoclonal antibody (rituximab) in second-line, or failed to splenectomy or subsequent relapse;
3. Subjects who received splenectomy or rituximab must have finished the therapy more than 3 months prior to UC-MSCs inclusion;
4. Platelet counts < 30×10^9^/L with bleeding;
5. Expected survival time for at least 6 months;
6. The function of liver and kidney is less than 1.5 times the upper limit of normal value, and the physical examination is qualified;
7. Subjects are allowed to maintain stable ITP concomitant treatment. The dose of glucocorticoids (less than or equal to 0.5mg/kg prednisone or equivalent dose of glucocorticoids) and thrombopoietin receptor agonists should be stable for at least 4 weeks, and the dose of azathioprine, danazol, cyclosporine A, mycophenolate mofetil, tacrolimus, and retinoic acid should be stable for at least 12 weeks;
8. Be able to understand the purpose and risks of the study and provide informed consent in accordance with national and local privacy regulations;
9. Cardiac function: Grade 2 or below according to the New York Society for Cardiac function;
10. ECOG physical status score ≤ 2.

## 6.2 Exclusion Criteria

1. Subjects with primary disease of important organs (liver, kidney, heart, etc.), or with immune system diseases;
2. Secondary thrombocytopenia caused by various reasons, such as connective tissue disorders, bone marrow hematopoietic failure disease, myelodysplastic syndrome, malignancy, drugs, inherited thrombocytopenia, common variable immune deficiency, lymphoma, etc.
3. Subjects infected with human immunodeficiency virus (HIV);
4. Uncontrollable and active infections during the screening period, including hepatitis B, hepatitis C, cytomegalovirus, EB virus, or positive syphilis antigen;
5. Subjects with extensive and severe bleeding, such as hemoptysis, upper gastrointestinal hemorrhage, intracranial hemorrhage;
6. Subjects with heart disease that requires treatment or hypertension that has been judged by researchers to be poorly controlled currently;
7. Subjects with any venous or arterial thrombosis, atherosclerosis, and other diseases;
8. Subjects with a history of malignant solid tumor or have received allogeneic stem cell transplantation or organ transplantation;
9. Subjects with mental disorders who are unable to sign normal informed consent and conduct trials and follow-up;
10. Subjects whose toxic symptoms caused by pre-trial treatment have not disappeared;
11. Subjects with other serious diseases that may limit their participation in this trial (diabetes; severe cardiac insufficiency; myocardial obstruction or unstable arrhythmia or unstable angina pectoris in the last 6 months; gastric ulcer; active autoimmune disease, etc.);
12. Subjects with septicemia or other irregular bleeding;

## Female subjects who are nursing or pregnant/suspected pregnant (positive pregnancy tests for human chorionic gonadotropin in urine during screening).

## 6.3 Method of Assigning to Groups

Join the group sequentially.

# 7. Number of Subjects

At least 15 patients are expected to be recruited.

Three dose groups will be set in the dose-escalation stage, 3 subjects will be enrolled each time and 9-12 patients will be enrolled in total according to the "3+3" dose-escalation protocol.

There will be 6 patients enrolled in the dose-expansion stage to explore the efficacy.

# Usage, Dosage, Time and Course of Umbilical Cord-derived MSCs

## 9.1 Usage and Dosage of Umbilical Cord-derived MSCs

1. Name of cell products: Umbilical cord-derived MSCs.
2. Specification: 5mL/bag, the main component is MSCs derived from human umbilical cord cultured in vitro, containing 2.0×10^7^ cells. The cell cryopreservation solution is a compound electrolyte solution containing 5% human serum albumin and 10% dimethyl sulfoxide (DMSO).
3. Usage of cell products: Divide into 3 dose-escalation groups (Group A, Group B, and Group C) in turn, with 3 subjects in each group and proceed sequentially from low dose to high dose group according to the principle of dose-escalation. The specific number of subjects in the group is based on a traditional "3+3" dose-escalation protocol, 3 subjects will be enrolled each time, and if no DLT occurs in 3 cases, the trial will be continued at the next level dose; if DLT occurs in 1 of 3 patients, 3 more patients will be enrolled in the current dose, and when no DLT occurs anymore, the trial will be continued at the next level dose. If 2 or more DLTs occur in the 3 or 6 patients, the dose escalation will be stopped, and the current dose will be determined as the MTD.
4. 3 dose-escalation groups- Group A, Group B, and Group C:

- The dose of each infusion in Group A is 0.5×10^6^ cells/kg, intravenous infusion, once a week for a total of 4 times;
- The dose of each infusion in Group B is 1.0×10^6^ cells/kg, intravenous infusion, once a week for a total of 4 times;
- The dose of each infusion in Group C is 2.0×10^6^ cells/kg, intravenous infusion, once a week for a total of 4 times;

According to the above test results, the investigator will determine a specific dose experimental group (one of Group A, B, or C), and expand the sample size of the subjects to 6 cases.

## 9.2 Infusion Process of Umbilical Cord-derived MSCs

Subjects should be given dexamethasone 5mg before the infusion to prevent infusion reactions.

Umbilical cord-derived MSCs are administered by intravenous drip, and the cells need to be resuscitated and diluted 5 times before infusion. The operation method is as follows:

1. Preparation of the required liquid: Aseptically operates in the ultra-clean workbench, extract 20ml/bag of compound electrolyte MG3 injection (Otsuka, 500ml/bag) with a syringe, cover the needle cap, and place them in the ultra-clean bench as a cell diluent for use.
2. Cell recovery: Take the aluminum box containing the cell freezing storage bag out of the refrigerant and quickly place it in a water bath of more than 2 liters at 40 °C (container: 160 mm × 90 mm × 15 mm rectangular box) to quickly melt the cell suspension in the storage bag. After the cell suspension is completely thawed, the cell freezing storage bag is taken out from the water bath, and this process should be completed within 2 minutes. Precautions for this process: Before thawing cells, the water temperature of the water bath shall not be lower than 37°C; during the cell recovery process, it is forbidden to apply mechanical pressure to the unthawed cells to accelerate the thawing process (e.g. pinching by hand); if multiple bags of cells are required, thaw bag by bag; dilution of the cell suspension must be performed immediately after thawing.
3. Cell suspension dilution: After taking out the cell freezing storage bag from the water bath, the cell suspension dilution process is completed aseptically in the ultra-clean workbench. Use dry sterile cotton balls or sterile gauze to wipe off the moisture on the outer surface of the cell freezing storage bag and the mouth of the tube, and then sterilize the tube mouth of the freezing storage bag according to the routine disinfection of infusion. Inject the prepared 20 ml cell diluent slowly through one of the tubes and remove the syringe. Seal the tube mouth with sterile tape, bring the prepared cell bag to the beds as soon as possible, and gently shake the bag to mix the liquid in the bag.
4. Administration: Hang the cell freezing storage bag on the infusion stand, and use a disposable blood transfusion device for intravenous drip in accordance with routine blood transfusion requirements. The initial 10ml infusion rate is 2ml/min, and the remaining volume should be instilled at 4ml/min.
5. Line flushing: Transfer the blood transfusion device to normal saline injection, continue to infuse about 20-50ml intravenously, and completely infuse the remaining cell suspension in the line into the body, and the administration is completed.
6. Notes: all enrolled subjects should use umbilical cord MSCs prepared from the passage cell bank derived from the primary cell of the same donor.

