Traditional therapies of ITP in adults include first-line treatments (glucocorticoids with or without intravenous immunoglobulin (IVIG)) and second-line treatments (thrombopoietin (TPO), TPO receptor agonists, splenectomy, and immune-suppressive agents (such as Rituximab, Vincristine, and Azathioprine)). As one of the most common hemorrhagic diseases, ITP has a poor response to the current treatment and most patients need long-term medication maintenance treatment to alleviate bleeding symptoms, which seriously affects their quality of life and increases the economic burden on patients. Therefore, for adult ITP patients, especially refractory ITP patients, there is an urgent need for new treatments of solutions to solve this clinical dilemma. At present, some studies at home and abroad have tried to utilize the immunomodulatory function of MSCs to treat ITP patients and achieved certain effects. However, these results are all from small-sample case reports, and lack of credibility. Therefore, we designed this clinical trial to provide a definite clinical basis for the treatment of refractory ITP with UC-MSCs.

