## 9.4 Treatment Course

Infusions will be administered one time a week, a total of 4 times, and a course is 28 days.

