## 10.2 Prevention and Management of Infusion-related Reactions

Subjects should be given dexamethasone 5 mg before infusion of umbilical cord-derived MSCs to prevent infusion reactions.

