## 11.2 Administration Period (0d--4w):

Subjects are allowed to maintain stable ITP treatment according to the Chinese ITP treatment guidelines at the beginning of the study, including but not limited to glucocorticoids, thrombopoietin receptor agonists, azathioprine, danazol, cyclosporine A and mycophenolate mofetil, tacrolimus, retinoic acid, etc., and the dose of the above drugs should not be increased;

Among them, the dose of steroids and thrombopoietin receptor agonists should be stable for at least 4 weeks, and the dose of azathioprine, danazol, cyclosporine A, mycophenolate mofetil, tacrolimus, and retinoic acid should be stable for at least 12 weeks;

The start of other drugs for platelet elevation therapy is prohibited, including but not limited to thrombopoietin receptor agonists, rituximab, CD38 monoclonal antibody, and other clinical trial drugs, to avoid a significant impact on efficacy analysis of the umbilical cord-derived MSCs;

Concomitant ITP medications can be reduced or phased out if subjects have a platelet count ≥50×10^9^/L for at least 2 weeks according to Chinese ITP Guidelines or medical routine.

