| **Window period** |  |  | **±**  **2D** | **±**  **2D** | **±**  **2D** | **±**  **2D** | **±**  **2D** | **±**  **2D** | **±**  **2D** | **±**  **2D** | **±**  **2D** | **±**  **2D** | **±**  **2D** | **±**  **2D** | **±**  **2D** | **±**  **2D** | **±**  **2D** | **±**  **2D** | **±**  **5D** | **±**  **5D** | **±**  **5D** |
| **ECG** | **√** |  |  |  |  |  |  |  |  |  |  |  |  |  |  |  |  | **√** |  |  |  |
| **Chest x-ray** | **√** |  |  |  |  |  |  |  |  |  |  |  |  |  |  |  |  | **√** |  |  |  |
| **B-ultrasound [5]** | **√** |  |  |  |  |  |  |  |  |  |  |  |  |  |  |  |  | **√** |  |  |  |
| **Adverse events** |  | **√** | **√** | **√** | **√** | **√** | **√** | **√** | **√** | **√** | **√** | **√** | **√** | **√** | **√** | **√** | **√** | **√** | **√** | **√** | **√** |
| **Infusion time of MSC** |  | **√** | **√** | **√** | **√** |  |  |  |  |  |  |  |  |  |  |  |  |  |  |  |  |
| **Pharmacokinetic study [6]** |  | **√** |  |  |  |  |  |  |  |  |  |  |  |  |  |  |  |  |  |  |  |
| **Detection of MSC antibody [7]** | **√** |  |  |  | **√** |  |  |  |  |  |  |  |  |  |  |  |  |  |  |  |  |
| **Immune function monitoring [8]** | **√** |  |  | **√** |  | **√** |  |  |  | **√** |  |  |  | **√** |  |  |  | **√** |  | **√** |  |

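### With dexamethasone before every infusion and no control arm, early platelet and immune results estimate premedication plus UC-MSC, yet Section 14.2 credits them to the cells

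*Protocol*

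**What the plan says.** Section 9.2 states: "Subjects should be given dexamethasone 5mg before the infusion to prevent infusion reactions". Section 10.2 repeats it ("Subjects should be given dexamethasone 5 mg before infusion of umbilical cord-derived MSCs to prevent infusion reactions") and the synopsis says the same. Section 9.4 sets the course: "Infusions will be administered one time a week, a total of 4 times, and a course is 28 days". The flow chart row "Infusion time of MSC" is ticked at D1, W1, W2 and W3.

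The protocol also treats this drug class as active against ITP. Section 2 puts glucocorticoids in first-line therapy. Section 11.2 lists them among the concomitant ITP treatments that may continue during the administration period, "and the dose of the above drugs should not be increased". Section 11.5 names them as emergency treatment. Section 11.2 further bars starting other platelet-raising drugs, "to avoid a significant impact on efficacy analysis of the umbilical cord-derived MSCs". Nothing says how the premedication relates to these rules.

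On efficacy:
- Section 3.2, endpoints 2 and 3, need one qualifying count; endpoint 3, for example, asks for a "2-fold increase from baseline at least once" together with a platelet threshold.
- Endpoint 4 runs from the first infusion to the first count of at least 50×10^9/L.
- Section 14.2 takes a rise in platelets after infusion as evidence that the product is effective, and confirms CR or R by two tests at least 7 days apart.
- Section 13.3 counts subjects who respond before finishing the infusion course as responders.

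**The concern.** The protocol keeps other platelet-raising drugs out of the administration period so that a rise can be read as an effect of the cells. It then gives a drug from a class that it calls ITP therapy to everyone, on the same days as the cells. Section 5.1 describes a single-arm study, so no comparison inside the trial can separate the two. This is planned exposure of all subjects and not rescue, so rules for handling rescue do not reach it.

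What is at stake is the interpretation of early efficacy. A transient rise caused by the steroid during the infusion weeks could satisfy a single-count endpoint, shorten the time to 50×10^9/L or be confirmed as a response, and would be reported as UC-MSC efficacy. Early changes in immune function carry the same ambiguity.

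**Working it through.** **1. Exposure.** Sections 9.2 and 10.2 are read as applying to each infusion, which is their natural sense. Four infusions × 5 mg = 20 mg, at D1, W1, W2 and W3. The documents give no steroid conversion, so this is not compared with the permitted background dose.

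**2. Counts close to a dose.** After D1 the flow chart schedules platelet counts at W1 to W16 (16 visits) and at W20, W24 and W28 (3 visits): 16 + 3 = 19. W1, W2, W3 and W4 each fall about 7 days after a dose: 4/19 = 21%. The other 15 are further away. Gaps from the last dose at W3, allowing ±2 days at both visits (±4 in total):
- W4: 7 days nominal, range 3 to 11
- W5: 14 days nominal, range 10 to 18
- W6: 21 days nominal, range 17 to 25

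**3. Which results can be decided inside W1-W4.**
- Endpoints 2 and 3: yes, since one count is enough.
- Endpoint 4: yes, since its clock starts at the first infusion.
- CR or R: yes. W1 and W3 are nominally 14 days apart and at least 14 − 4 = 10 days apart after windows, so the 7-day confirmation rule can be met within the infusion weeks.
- Endpoint 7 (longest run at or above 30×10^9/L): partly. A run can start there, but a long one must extend beyond.
- Immune samples (Section 8): the one before the third infusion follows at least two doses. The 4-week one follows all four, the last about a week earlier.

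**4. What the estimate contains.** Section 5.23 reports proportions with 95% confidence intervals. In a single arm, such a proportion estimates the probability of response under background treatment, premedication and cells together. The interval describes sampling error around that quantity and contains nothing that isolates the cells.

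**5. Sample size.** The stated minimum reproduces: 3 groups × 3 + 6 expansion = 15. No null response rate or power is given, so there is no benchmark against which to read an early response.

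**6. Illustration only.** Suppose the cells did nothing and premedication alone produced an early qualifying count with probability p. The range of p from 5% to 30% is an assumption without support in the documents. Expected responders = n × p; P(at least one) = 1 − (1 − p)^n.
- n = 6 (expansion): expected 6 × 0.05 = 0.3 to 6 × 0.30 = 1.8. P = 1 − 0.95^6 = 0.265 to 1 − 0.70^6 = 0.882.
- n = 15: expected 15 × 0.05 = 0.75 to 15 × 0.30 = 4.5. P = 1 − 0.95^15 = 0.537 to 1 − 0.70^15 = 0.995.

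If p is zero, all of these vanish. The point is only that the planned proportions could not show which case applies.

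**The case against.** Several objections have force.

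- **A reader might infer that the protocol forbids its own premedication.** The text does not go that far. The no-increase rule in Section 11.2 concerns the subject's stable ITP treatment, while the dexamethasone is mandated for another stated purpose. This is an overlap that nobody has reconciled, not a flat contradiction.
- **A reader might infer an inflated false-positive rate for a before-after platelet test.** No such test is planned. Section 5.23 is mainly descriptive and its tests compare groups. The only before-after P value, in Section 14.2, concerns heart, liver and renal function. Rejection rates for a paired test would describe an analysis outside the plan.
- **A reader might infer that the choice of expansion dose is biased.** The premedication is a fixed 5 mg in every dose group, so it cannot by itself favour one.
- **The population responds poorly to steroids.** Section 6.1 requires insufficient response to first-line drugs, with splenectomy failure as an alternative route, and allows stable background glucocorticoids. This makes a steroid effect less likely, but insufficient response is not the same as none.
- **Counting weeks from the end of treatment.** The synopsis and part of Section 14.1 list platelet counts from 1 week after the four infusions. Section 14.1 also requires weekly counts in the first month after the first infusion, and the flow chart includes W1-W4, so the early counts exist.
- **The later window is less protected.** Section 11.3 does not repeat the ban on new platelet-raising drugs and allows retreatment on recurrence. This stands, and it is why later counts should supplement the planned analysis and not replace it.
- **Sensitivity analyses may sit in an SAP.** True, and the absence of one here is not the fault. An SAP cannot, however, change the attribution in Section 14.2 or reconcile the protocol's own sections.

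**Conclusion.** The concern holds for early results. Endpoints 2, 3 and 4, CR or R confirmed within W1-W4, and the two early immune samples estimate the regimen of premedication plus UC-MSC; Section 14.2 goes too far in crediting a rise to the cells. About a fifth of the scheduled counts after D1 (4 of 19) are directly exposed. Counts sustained through later visits are much less open to this explanation, so the efficacy data as a whole are not invalidated.

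The size of any dexamethasone effect is unknown from the documents, and nothing here shows that there is one. Efficacy is a secondary, preliminary objective and the primary safety objective is not at issue. The conclusion rests on two readings: that the premedication precedes each infusion, and that visits follow the flow chart. The change is worth making because it is cheap and because the protocol itself sets out to exclude this kind of influence.

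**What to change.** 1. Reconcile Sections 9.2 and 10.2 with Section 11.2 by stating how the premedication relates to the no-increase rule. This is clarification only; clinical management stays with the clinicians.
2. In Sections 5.23 and 14.2, keep the planned analysis and add a supportive one of endpoints 2, 3, 4 and 7 and of CR/R. It should count only platelet values after the infusion weeks, for example from W5 or W6 on; the choice is a judgement and should be fixed in advance. For endpoint 4 this means the first qualifying count in the window, and for endpoint 7 the part of a run that lies in it. Counts after emergency treatment, retreatment or newly started platelet-raising drugs should not be credited.
3. State in Section 14.2 that responses seen only in W1-W4, and the immune changes before the third infusion and at 4 weeks, are attributed to the regimen including premedication and not to UC-MSC alone.

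The cost is wording and one extra table. The visits already exist, and Section 11.5 and the flow chart already provide for recording concomitant medication. The downside is that a true early response lost before the window is not credited in the supportive analysis; it remains visible in the planned one.
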